#### MOVI-HIIT! programme: description

2.3.1

The design of the MOVI-HIIT intervention was grounded in the socio-ecological model of behaviour change, addressing factors at the individual, family, and school levels (25). The programme was implemented over one academic year (October 2022 to May 2023) and consisted of two daily 6-minute classroom-based ABs involving physical exercise based on HIIT principles, following a 20"/10" work-to-rest ratio. ABs were delivered through a virtual platform (http://www.movihiit.es) guided by animated avatars, and required no specific equipment, as all classrooms were equipped with interactive screen and internet access.

Each AB followed a structured format: approximately 1 min of animation and exercise explanation, 4 min of physical exercise based on HIIT, and 1 min of breathing and relaxation exercises to facilitate the transition back to academic tasks. The HIIT phase consisted of four exercises (e.g., squats, jumping jacks, or running in place), performed at high intensity (80%–90% of maximum heart rate) for 20 s, interspersed with 10-second recovery periods (65%–75% of maximum heart rate). The sequence of four exercises was repeated twice Figure 2.

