#### MOVI-HIIT! organization and delivery

2.3.2

The intervention programme was designed by graduates in Sport and Exercise Sciences, together with Physical Education teachers, and was implemented by the classroom tutors at each participating school. At the beginning of the intervention, teachers attended a 4-hour training workshop in which the research team presented the materials and the virtual platform and provided detailed guidance on their use. In addition, teachers were given a one-week familiarisation period with the programme under the supervision of the research team. To respect teachers’ autonomy and facilitate the integration of the intervention into classroom routines, teachers were allowed to choose the most suitable time of day to implement the HIIT breaks. However, team members recommended carrying them out when schoolchildren (i) had been sitting for a long time, (ii) were not paying attention, or (iii) seemed tired from academic tasks.

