School-day assessment. To assess PA during school hours, an independent subsample of 150 children from both study groups wore a GENEActiv Original accelerometer (ActivInsights, UK) on the non-dominant wrist from 09:00 to 14:00 during two measurement waves (September–November 2022 and April–May 2023). Devices were initialized at 30 Hz with a ± 8 g dynamic range and recorded raw triaxial acceleration in g. Raw accelerometer data were processed in R (version 4.3.2) using the GGIR package (version 3.0.0) (38), including and initial autocalibration step based on local gravity and temperature according to the algorithm described by van Hees et al. (38). Non-wear time was identified using the standard deviation and range of raw acceleration signals over 60-minute windows with 15-minute increments, following the default GGIR approach (39). Due to the short monitoring duration, physical activity was derived as ActiGraph-equivalent activity counts from raw acceleration using the actilifecounts package (version 1.1.1) (40), according to the method proposed by Neishabouri et al. (41), with a 5-second epoch length. Activity intensity was categorized as sedentary (<306 counts/5 s), light (306–817 counts/5 s), moderate (818–1968 counts/5 s), and vigorous (≥1969 counts/5 s) using the vector magnitude cut-points validated by Chandler et al. for wrist-worn accelerometers in children (42). The school day was analyzed between 09:30 and 13:30 to exclude arrival and departure times, and a valid school day was defined as at least 3 h of wear time within this period after exclusion of non-wear.

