Another limitation identified was that, although teachers were allowed to choose the timing of ABs to facilitate their implementation, the exact time of their implementation was not systematically recorded as a quantitative variable; therefore, possible differences according to the time of day could not be examined. Finally, the implementation of similar ABs in the control group was not formally monitored or objectively recorded; therefore, some degree of contamination could not be completely ruled out.

In conclusion, the MOVI-HIIT study presents an innovative and potentially scalable model for integrating HIIT-based ABs into preschool classrooms through a gamified digital platform. By detailing the prespecified methods and implementation strategy, this article aims to support transparency and reproducibility, and to inform future school-based interventions. The study will provide insights into the potential effects of HIIT-based ABs on body composition, fitness, and executive function, alongside teachers’ perspectives on implementation, which may help guide future educational practice and health policy to foster active and healthy school environments.

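### School-day activity is analysed only from 09:30 to 13:30 although teachers chose the break times, so breaks in the outer half hours would drop out of the outcome in the intervention arm only

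*Protocol article*

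**What the plan says.** Section 2.4.2.1 of the Protocol article (school-day assessment) states the aim and the sample: "To assess PA during school hours, an independent subsample of 150 children from both study groups". The device was worn "on the non-dominant wrist from 09:00 to 14:00 during two measurement waves (September–November 2022 and April–May 2023"). The analysis period is shorter: "The school day was analyzed between 09:30 and 13:30 to exclude arrival and departure times". The wear criterion applies inside that shorter period: "a valid school day was defined as at least 3 h of wear time within this period after exclusion of non-wear".

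The programme, in section 2.3.1, "consisted of two daily 6-minute classroom-based ABs involving physical exercise based on HIIT principles". On timing, section 2.3.2 says that "teachers were allowed to choose the most suitable time of day to implement the HIIT breaks". It adds advice, not a rule: "team members recommended carrying them out when schoolchildren (i) had been sitting for a long time", or when they were inattentive or seemed tired from academic work. No section restricts the breaks to 09:30–13:30.

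The Discussion concedes that "the exact time of their implementation was not systematically recorded as a quantitative variable". It draws one consequence, that differences by time of day cannot be studied. It does not link the gap to the school-day activity outcome. Section 2.3.3.1 says the platform logged the number of sessions per class by week and month. It does not say whether a clock time was kept with each session.

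**The concern.** Of all the trial's outcomes, school-day activity is the one closest to the intervention: the breaks are themselves physical activity in school hours. Trimming arrival and departure removes ordinary movement from both arms alike. Trimming a programme break removes activity from the intervention arm alone, because control schools had no programme breaks. If some teachers used the first or last half hour, part of the activity that the programme added is missing from the comparison meant to show it.

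The signal is small, at most 8 minutes of exercise phase a day in a 240-minute window, so one displaced break matters. Timing was a teacher's choice, so any loss may be habitual and concentrated in particular classes, and need not average out. With the trimmed window alone, a reader who sees a small difference cannot judge whether break timing contributed.

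**Working it through.** The article gives no figure for this point to reproduce. The check is interval arithmetic, with break timing as an explicit assumption.

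**Inputs from the article**
- Wear period 09:00–14:00: 300 min (2.4.2.1).
- Analysed window 09:30–13:30: 240 min, which is minutes 30 to 270 after 09:00 (2.4.2.1).
- Two breaks a day of 6 min each: about 1 min introduction, 4 min exercise, 1 min relaxation (2.3.1).
- Exercise phase: four exercises done twice, so 8 bouts of 20 s work and 10 s recovery (2.3.1).

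**Step 1. Time removed.** 300 − 240 = 60 min, and 60/300 = 20% of the recorded period, half at each end.

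**Step 2. Daily dose.** Exercise phase: 2 × 4 = 8 min. Work bouts only: 2 × 8 × 20 s = 320 s = 5.3 min. Relative to the window, 8/240 = 3.3%.

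**Step 3. Exercise lost under different timings.** Let a break start s minutes after 09:00. Its exercise runs from s + 1 to s + 5, and the latest start that ends by 14:00 is s = 294.
- *No break in the outer half hours:* loss 0%.
- *s uniform on 30 to 294 (first half hour not used):* exercise is fully inside for s from 30 to 265, giving 235 × 4 = 940. Over the next 4 minutes of start times the overlap falls from 4 to 0, adding ½ × 4 × 4 = 8. Mean retained = 948/264 = 3.59 of 4 min. Loss = 1 − 3.59/4 = 10%, or about 0.8 of 8 min a day.
- *s uniform on 0 to 294:* mean retained = 4 × 240/294 = 3.27 of 4 min. Loss = 1 − 240/294 = 18%, or about 1.5 of 8 min a day.
- *A class that always holds one break in an outer half hour:* loss 4/8 = 50%.
- *Both breaks there:* loss 100%, all 8 min.

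**Step 4. Scale.** These losses are in minutes per day. The article does not say whether the outcome is minutes or a share of wear time. As a share, under fully uniform timing, the added exercise is 8/300 = 2.7% of the full period and 8 × 240/294 = 6.5 min, 6.5/240 = 2.7%, of the trimmed one: almost unchanged. On that scale, attenuation needs breaks to cluster in the outer half hours.

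**The case against.** The strongest reply is that the window has a stated and sensible purpose and that no section shows a single break outside it. Breaks are described in the Introduction as integrated into lessons, and arrival and departure are poor moments for a class-wide activity led from a screen. The advice to teachers points away from 09:00–09:30, since children have not yet sat long or tired. This stands. It is why the scenarios start at 0% and why one of them leaves out the first half hour. It does not settle the last half hour, when tiredness might favour a break, and the advice was not binding.

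A second reply is that the 24-hour accelerometry in 250 children is not cut to this window. That is true, but it ran only from February to May 2023, so it has no pre-intervention measurement, and it uses a different device and different cut-points. It is supporting evidence, not a substitute.

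Third, a condensed article may leave sensitivity analyses to the full analysis plan. Accepted: the absence of one is not the fault. The point rests on two choices the article does fix, the window and the free timing.

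A reader might also infer that the wear rule is defective because a day with no break inside the window still counts as valid. It is not. The analysis is by intention to treat, days without a break belong in it, and a wear criterion is not meant to guarantee exposure.

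**Conclusion.** The point holds as a possible one-sided loss of unknown size. Any programme break held at 09:00–09:30 or 13:30–14:00 is excluded from school-day activity and sedentary time, and only in the intervention arm. The between-arm difference in minutes could therefore be attenuated.

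The plausible loss runs from 0%, through about 10% and 18% under the two uniform-timing assumptions, to 50% or more in a class with such a habit. The documents cannot narrow this range. The percentages assume that each break is delivered in full within wear time.

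A reader might infer more: that the comparison is biased towards no effect, that about a fifth of the dose is missing, or that a null result could never be interpreted. The documents do not support these readings. No break is shown to have fallen outside the window, the 18% comes wholly from assumed timing, and the full-period recordings allow the sensitivity of the result to the window to be examined.

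The outcome is secondary, measured in 150 children, in a trial sized on VO₂max. The point does not touch the primary outcomes. It merits a cheap improvement to the plan, not a change of design.

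**What to change.** Keep 09:30–13:30 as the main window. Add, before the analysis, a sensitivity analysis of the same outcomes over the full recorded 09:00–14:00 period, with wear time in the model. Report both estimates with confidence intervals on the same scale, including minutes per school day. Do not require the two to agree: such a rule has no defined threshold and would let arrival and departure movement overrule the chosen window.

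Check whether the platform's session records carry a time stamp. If they do, report how many breaks on wear days fell outside 09:30–13:30. If they do not, extend the limitation in the Discussion on unrecorded break times to say that breaks in the outer half hours would be missing from school-day activity and sedentary time in the intervention arm.

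The cost is one more processing run on data already collected. The downside is extra noise from arrival and departure movement, which occurs in both arms.

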##### Active commuting to/from school

2.4.2.2

The Mode and Frequency of Commuting to and From School Questionnaire was administered to parents. This questionnaire has been previously validated against accelerometry in Spanish children and adolescents (43, 44). It includes four items assessing both the usual mode and the weekly frequency of commuting between home and school. Specifically, parents reported the usual mode of commuting by answering the following questions: (1) How does your child usually get to school? and (2) How does your child usually get home from school? Weekly frequency of commuting modes was assessed using the questions: (3) How does your child get to school each day? and (4) How does your child get home from school each day? Response options for all items were: (a) walking; (b) cycling; (c) car; (d) motorcycle; (e) school bus; (f) public bus; (g) subway/train/tram; or (h) other (with specification required). Active commuting to and from school was defined as regular travel by walking or cycling, whereas inactive commuting included travel by car, motorcycle, school bus, public bus, subway, train, or tram. In addition, parents reported their child's distance and time to school. Distance was assessed by the question: (1) How far from the school does your child live?, with response options: (a) < 0.5 km; (b) 0.5 to <1.5 km; (c) 1.5 to <3 km; (d) 3 to <6 km; and (e) ≥ 6 km. Travel time was assessed using the question: (2) How long does it usually take your child to get to school from home?, with response options: (a) < 5 min; (b) 5 to <15 min; (c) 15 to <30 min; (d) 30 to <60 min; and (e) ≥ 60 min (45).

##### Blood pressure

2.4.2.3

Blood pressure was measured twice, 5 min apart, after a minimum 5-minute rest period, with children seated in a quiet environment and the right arm slightly flexed at heart level. The mean of both readings was used for analysis. Measurements were obtained using an Omron® M5-I automatic monitor (Omron Healthcare UK Ltd.) with cuff sizes adjusted to arm circumference (46).

##### Health-related quality of life

2.4.2.4

Was measured using the Kiddy-KINDL questionnaire, a validated Spanish version of the KINDL questionnaire for children aged 4 to 7 years (47). The questionnaire consists of 6 dimensions on a 5-point Likert scale, with a total of 24 items, exploring physical, emotional, social and school aspects of childreńs lives. Children and their parents were asked to complete this questionnaire separately to compare results.

#### Confounding variables

2.4.3

The following possible confounding variables were assessed through a self-administered questionnaire completed by parents or legal guardians: sex, age, birth weight, gestational age, parental height and weight, area of residence (urban or rural), and country of origin. Additionally, other relevant variables were recorded:

Family socioeconomic status. Was assessed as in previous MOVI studies (48). Using a self-administered questionnaire on parental education and occupation. Education was classified into three levels: primary (no or incomplete primary education), secondary (primary or upper secondary education), and university (degree or doctorate). Occupation was grouped into five categories: (i) supervisor/manager or self-employed with ≥10 employees, (ii) supervisor/manager or self-employed with <10 employees, (iii) self-employed with no employees, (iv) unskilled worker, and (v) homemaker, unemployed, or other. A family socioeconomic status index combining both variables was then calculated, yielding five levels: lower, lower/middle, middle, upper middle and upper (49).

Food Consumption. The Spanish version of the validated questionnaire on children's eating habits was used for children aged 2 to 9 years. The questionnaire was completed by the parents (50).

Breastfeeding. Parents reported the type of feeding provided during the first 24 months of their child's life. For each month, mothers indicated whether the child received breast milk, formula, or both, and whether complementary foods were introduced. Based on this information, breastfeeding was classified into exclusive, mixed, or formula feeding, and the duration of each was recorded (51).

### Data analysis

2.5

#### Sample size

2.5.1

In a trial with multiple outcomes, the sample size was estimated using a prespecified reference outcome rather than calculating a separate sample size for each endpoint. Cardiorespiratory fitness (VO₂max, mL·kg⁻1·min⁻1) was selected as the reference outcome because it was one of the main study outcomes and the one for which the most robust assumptions were available from a previous comparable school-based cluster-randomized intervention conducted by our group (MOVI-2) (52). Based on that study, an effect size (Cohen’s d) of at least 0.2 was expected when comparing the IG with CG. However, since the study hypotheses focused on less physically fit schoolchildren—who might benefit more—an effect size of 0.3 was assumed.

The calculation was performed following the methods of Donner and Klar (53), using Optimal Design software, with the multi-site cluster randomized trials, treatment at level 2 option. An average of 40 children per school (cluster), a statistical power of 0.80, a significance level of 0.05, and an effect size of 0.3 were assumed. Under these conditions, a total sample size of 10 schools was estimated. An average of 40 children per school was considered under two assumptions: a) although the actual average was approximately 100 children per school, the main analysis focused on the 50% with the lowest baseline VO₂max levels by age and sex; and b) a dropout rate of 15% was anticipated. Although cognitive and adiposity outcomes were also assessed, the trial was not specifically powered for each individual endpoint; therefore, these results should be interpreted accordingly.

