In this context, exploring innovative approaches to enhance the effectiveness of ABs is particularly relevant. High-intensity interval training (HIIT) has emerged as a time-efficient and effective method to improve children's health and fitness, alternating short bouts of vigorous activity with brief recovery periods (18). However, although HIIT appears well suited to children's natural activity patterns (19), evidence on the effectiveness of HIIT interventions in children under 6 years of age remains limited. Classroom-integrated HIIT programmes have been scarcely studied in preschoolers, with insufficient evidence regarding their effects on physical fitness, body composition, and cognition. Therefore, developing an ABs programme grounded in HIIT principles could represent a promising approach to optimize its benefits in early childhood and to provide new evidence in this field.

On the other hand, integrating digital technologies into education can enhance students’ engagement and participation (20). When designed with interactive or gamified features, these tools, including screen-based resources, can encourage movement and support more active learning experiences (21). Therefore, exploring digital platforms to deliver HIIT-based ABs in preschool settings is particularly relevant, as to our knowledge no previous studies have implemented a gamified digital approach for this purpose.

The present study describes the rationale and prespecified methods of a cluster-randomized controlled trial (RCT) —the MOVI-HIIT study — aimed at: (i) evaluating the effectiveness of a classroom-based HIIT inspired AB intervention, delivered through a gamified digital platform, on preschool children's body composition, physical fitness, and executive function; and (ii) exploring teachers’ perceptions of barriers and facilitators to its implementation and monitoring through a nested qualitative study. The trial procedures and analyses are reported here to support transparency and reproducibility, in line with the purpose of a study protocol, while intervention outcomes will be reported separately.

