#### Statistical analysis

2.5.2

The statistical analysis will have three phases. The first will consist of verifying that randomisation was effective in creating two comparable groups of schoolchildren, exploring the presence of extreme values and outliers, and assessing the degree of fit of the main variables to the normal distribution.

In the second phase, mixed regression models will be used, taking each outcome variable as the dependent variable, the intervention as a fixed effect (1 = IG and 0 = CG), adjusting for baseline values, age, sex, and including school (cluster) as a random effect. Given that this is a cluster-randomized trial, randomization is the main strategy to minimize selection bias, whereas covariate adjustment is intended primarily to improve precision and account for chance baseline imbalances. The results will be expressed as absolute differences in the changes in the variables between baseline and final measurements [95% confidence interval (95%CI)]. For binary outcomes (e.g., overweight/obesity), logistic regression models will be used, and odds ratios with their 95% CIs will be reported.

In the third phase, a sensitivity analysis will be performed to verify whether the results, using a different variable adjustment method, have the same direction and similar magnitude. To do this, the IG and CG will be compared using the propensity score statistical method to account for the imbalance of covariates in baseline measurements between clusters. The propensity score estimates the effect of the intervention using a causal inference model, explaining what would have happened if all subjects in the IG and CG had the same characteristics at the start of the study. Each subject is matched to a subject with similar characteristics using a caliper of 0.40 using the psmatch2 command.

All analyses will be conducted on an intention-to-treat basis, maintaining participants in their originally assigned IG or CG, regardless of the number of active-HIIT breaks they received, and considering the CONSORT recommendations for this specific type of cluster design (54). In addition to analyses for the total sample, subgroup analyses by age, sex, and socioeconomic status will be conducted.

However, to assess adherence to the intervention, data will be collected on the number of active HIIT breaks each group received. Children in classes that delivered ≥80% of the scheduled breaks will be considered to have received the intervention.

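### The sample size rests on a main analysis of the less-fit half of children, but the analysis plan never includes that half, so the stated 80% power does not describe the analysis as written

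*Protocol article*

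**What the plan says.** **Section 2.5.1 (Sample size).** The reference outcome is VO2max. From a previous school-based trial by the same group, a Cohen's d "of at least 0.2 was expected when comparing the IG with CG". This is raised to 0.3 "since the study hypotheses focused on less physically fit schoolchildren", who might benefit more. The calculation is then described: "a statistical power of 0.80, a significance level of 0.05, and an effect size of 0.3 were assumed", with an average of 40 children per school, giving 10 schools. The 40 is explained by two things. Although "the actual average was approximately 100 children per school", "the main analysis focused on the 50% with the lowest baseline" VO2max by age and sex; and 15% dropout is allowed for.

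**Section 2.5.2 (Statistical analysis).** Mixed models are planned for every outcome, adjusted for baseline value, age and sex, with school as a random effect. No restriction by baseline fitness is given. On populations, the section says: "In addition to analyses for the total sample, subgroup analyses by age, sex, and socioeconomic status will be conducted". No fitness-defined group is listed.

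**Introduction (aims).** The first aim is "evaluating the effectiveness of a classroom-based HIIT inspired AB intervention, delivered through a gamified digital platform", in preschool children without restriction to the less fit.

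**The concern.** Two current, adjacent sections do not fit together. Section 2.5.1 identifies a main analysis population and takes both of its key inputs from it. Section 2.5.2, which sets out what will be fitted and in whom, leaves that population out both as the main set and as a subgroup.

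Two things are at stake. First, the 80% power belongs to a comparison that the analysis section does not contain. Second, two VO2max results, one in the less-fit half and one in all children, could each be presented as the main one with support from this text. Final measurements were taken in June 2023, and the article still describes the analyses in the future tense. Leaving the confirmatory population open after the data exist weakens whichever result is put forward.

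**Working it through.** **1. How far the design depends on the less-fit half.** The effect size moves from 0.2 to 0.3 only because of it. The cluster size also follows from it: 100 × 0.5 × (1 − 0.15) = 42.5, taken as about 40. Without the restriction, the same rule gives 100 × 0.85 = 85 per school. Neither d = 0.3 nor 40 per school has a stated basis for the total sample.

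**2. The plan's own figure.** The article states no ICC, so the 10 schools can be neither confirmed nor refuted. I used a two-arm cluster comparison in SD units:

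- SE² = (ICC + (1 − ICC)/m) × (1/J1 + 1/J2)

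Here m is children per school, and J1 and J2 are schools per arm. With 5 v 5 schools, m = 40 and ICC = 0, SE = √(0.025 × 0.4) = 0.100 and d/SE = 0.3/0.100 = 3.0. Two-sided power at 5% is 85% with a normal reference and 75% with t on 8 df. The normal reference gives 80% at an ICC of about 0.004.

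**3. The two populations as the trial was run.** Inputs: nine schools, 5 v 4 (section 2.1), and 522 children (Abstract), so 522/9 = 58 per school and about 29 in the less-fit half. 1/5 + 1/4 = 0.45. Power comes from the noncentral t on 7 df (critical value 2.365), two-sided 5%, without gain from covariates. The ICC values are assumed.

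| ICC | Total: SE | Total: d/SE (d = 0.2) | Total: power | Half: SE | Half: d/SE (d = 0.3) | Half: power |
|---|---|---|---|---|---|---|
| 0 | 0.088 | 2.27 | 50% | 0.125 | 2.41 | 55% |
| 0.02 | 0.129 | 1.55 | 27% | 0.156 | 1.93 | 38% |
| 0.05 | 0.173 | 1.16 | 17% | 0.193 | 1.55 | 27% |

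Example, total sample at ICC = 0.02: 0.02 + 0.98/58 = 0.0369; √(0.0369 × 0.45) = 0.129; 0.2/0.129 = 1.55.

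The difference between populations is about 5, 11 and 10 percentage points.

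**4. Type I error if either population may be called main.** The half is nested in the whole, so the correlation of the two test statistics is

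- r = √[(ICC + (1 − ICC)/58) / (ICC + (1 − ICC)/29)]

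This gives 0.71, 0.83 and 0.90 at ICC 0, 0.02 and 0.05. Under a bivariate normal null, the probability that at least one |z| exceeds 1.96 is 8.3%, 7.6% and 7.1%.

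**The case against.** **Section 2.5.2 declares no rival primary population.** This is correct. It mentions total-sample analyses and lists subgroups, but calls none of them main. The defect is that the population named as main in 2.5.1 is missing from 2.5.2. A reader might infer that the less-fit half will certainly go unreported; the text does not establish that.

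**The less-fit half might seem to conflict with intention to treat.** It does not. Section 2.5.2 defines intention to treat as keeping children in their allocated arm regardless of breaks received. A subset defined by a baseline measurement is compatible with that.

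**The article says at least 0.2.** This also stands. Power at exactly 0.2 is the least favourable reading of the article's expectation for the total sample.

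**The low power is mostly not due to the mismatch.** This stands too. The less-fit half as run reaches only 55%, 38% and 27% under the same method. Most of the gap from 80% comes from the small number of schools, the few degrees of freedom and the assumed ICC.

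**An unseen analysis plan could settle the population.** It could, but this article would still contradict itself, because it does state analysis populations in both sections.

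**Baseline adjustment might seem to cover the less-fit half.** It does not. The adjusted model estimates an average effect over all children, and 2.5.2 contains no term for a different effect in the lower half.

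**Conclusion.** The point holds as a conflict between sections 2.5.1 and 2.5.2. The sample size, effect size and 80% power refer to a main analysis of the less-fit half. The analysis section and the aims do not contain that analysis, and the confirmatory VO2max result is not identified. This conclusion rests on the text alone and needs none of the computed figures.

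The power figures are illustrations. They assume an ICC between 0 and 0.05, equal school sizes, no covariate gain, and effects of exactly 0.2 and 0.3. They show that the mismatch accounts for roughly 5 to 11 points of power, not for the whole shortfall from 80%. The type I error of about 7–8% is what free choice between the two populations would produce. A reader might infer that such a choice has been or will be made after seeing results; the documents give no evidence of that.

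**What to change.** Name one primary population in section 2.5.2 and bring section 2.5.1 and the aims into line with it. Two routes are open, and the choice is the sponsor's:

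- **(a) Less-fit half primary.** State this in 2.5.2 and in the aims, define the age- and sex-specific VO2max cut on both arms pooled, and label the total sample secondary.
- **(b) Total sample primary.** Restate the power in 2.5.1 for the total sample at d = 0.2 with the ICC that was used. List the less-fit half in 2.5.2 as a prespecified subgroup. Describe d = 0.3 as the effect expected within that subgroup. It should not be presented as the basis of an interaction test, because an effect within a subgroup is not a difference between subgroups.

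The article should also say when the choice was fixed relative to access to the outcome data. The cost is wording in the two sections and, under (a), in the aims; no new data are needed. The downside is that the stated power is likely to become less favourable.
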